**Fig. 1 Fig1:**
[figure not shown]
Flow chart

### Sample size

Sixty eligible young people will be randomised all together. The sample size is not based upon estimation of efficacy but is in keeping with published suggestions [29] and believed to be practically possible within the limits of the project. Further, it should enable us to assess rates of recruitment and retention to a reasonable degree of precision; assuming an attrition rate of around 20%, a sample of 60 would provide an estimate with 95% confidence interval of width 20% (i.e. +/− 10%). For a recruitment rate of around 50%, the interval width would be around 25% (i.e. +/− 12.5%).

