### Recruitment procedure

Young people will be triaged and assessed by the referring service according to each service’s standard procedures. If this assessment identifies low mood as a presenting difficulty, the case will be discussed with a clinical member of the research team (without identifying the young person) to ascertain likely suitability for the trial. Potentially suitable young people (and/or parents/carers if under 16) will be invited to participate. If they express an interest, consent will be given to the service to pass on their details to the research team. We are requesting teams only pass potential cases to the trial if therapy in both IPC and TAU can start within a couple of weeks of the baseline assessment, so differential waiting times do not bias results.

Those who express an interest will be contacted by the trial’s research practitioner who will further explain the study, answer any queries and provide copies of participant information sheets. Potential participants will be given at least 48 h to read and consider the information before being asked for consent.

If the young person wishes to participate following this process, the research practitioner will arrange a meeting at a convenient venue (e.g. their home address, school/college or a community venue), where the young person will be asked to complete a consent form (if 16 or over) or assent form (if under 16) at the start of the first research assessment to document the informed consent/assent process and their willingness to participate. For young people under 16, in addition to the child’s assent to participation, the consent of a parent or carer (adult with parental responsibility) will be required for the young person to be included in the study. Consent to participate in an interview as part of the process evaluation will be sought during the main consent procedures. However, it will not be a requirement that a young person/parent consents to a process evaluation interview in order to be included in the study.

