After informed consent has been appropriately obtained, participants will be asked to complete all baseline assessment measures. Only those who meet the eligibility criteria outlined above will be randomised. It is envisaged that a close liaison between the research practitioner and referring teams, and the subsequent telephone conversation with potential participants before baseline visit will ensure most referrals will conform to the eligibility criteria before the baseline assessment. However, in cases (which will be rare) where young persons do not meet the eligibility criteria after baseline assessment, it will be conveyed to them sensitively, and the research practitioner will liaise with the referring team to ensure the appropriate service is sought for the young person.

All staff members to be trained in the intervention will be given a verbal explanation of the objectives of the study, what he or she will be asked to do if they choose to participate and the possible risks and benefits of participation. Participation in the trial is not a condition of training. Participation in the process evaluation (listening to audiotapes of therapy and/or focus groups) is optional; staff will be given participant information sheets and asked for informed written consent to take part. Figure 1 is a flowchart diagram for this study.

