### Analysis

#### Statistical

Recruitment and retention rates will be estimated with 95% confidence intervals (CIs). Assuming sufficient information, time until drop-out will be analysed using ‘time-to-event’ methods, i.e. in an effort to identify baseline factors likely to be related to drop-out. The proposed primary outcome measure for the definitive RCT is the RCADS depression score at 10 weeks. Although the proposed study is not designed to assess efficacy, the mean between-group difference will be estimated using a general linear model including baseline RCADS depression score and treating therapist as a random effect. A 95% CI will be constructed to assess whether the treatment benefit is feasibly greater than the minimal clinically significant difference, i.e. whether or not it is included within the CI. A similar approach will be undertaken for the secondary outcome measures. The rate of completion of each outcome measure will be reported. If appropriate, depending on the proportion of missing values, multiple imputation will be undertaken and between-group differences re-estimated as a sensitivity analysis. Further parameters, such as within group variation, needed for the design of a subsequent full-scale trial, will also be estimated. All statistical analysis will be undertaken using STATA.

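### The precision quoted for a 50% recruitment rate (±12.5%) rests on a denominator of about 60, but 60 is the number randomised; the design gives about ±9% (minor, conservative)

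*Protocol article*

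**What the plan says.** The Sample size section of the protocol article opens with the number to be randomised: "Sixty eligible young people will be randomised all together". It bases this number on published suggestions and on what is practical within the project. It then adds that 60 should allow recruitment and retention to be estimated with reasonable precision, and gives two figures:

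- Attrition: "assuming an attrition rate of around 20%, a sample of 60 would provide an estimate with 95% confidence interval of width 20" per cent, that is ±10%.
- Recruitment: "For a recruitment rate of around 50%, the interval width would be around 25" per cent, that is ±12.5%.

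The first figure names its sample of 60. The second names no sample of its own.

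The Statistical analysis section commits to reporting both quantities: "Recruitment and retention rates will be estimated with 95% confidence intervals (CIs").

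The Recruitment procedure section describes the pool that feeds the trial. After triage and an anonymous case discussion, "Potentially suitable young people (and/or parents/carers if under 16) will be invited to participate". Those interested are contacted, consented and assessed at baseline, and then "Only those who meet the eligibility criteria outlined above will be randomised". The article gives no number for those invited, consented or assessed.

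**The concern.** A recruitment rate is the number randomised divided by the number in some larger pool from which they came. The 60 randomised are the top of that fraction. The quoted ±12.5% looks as if the 60 had been carried over from the attrition calculation and placed at the bottom. If so, the paragraph disagrees with itself: a 50% rate among 60 approached yields 30 randomised, not the 60 in its first sentence.

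What is at stake is limited but real. Feasibility of recruitment is part of the first question in Aims and objectives, and the precision statement tells the reader how well the trial will answer it. An error bar that the design does not have should be corrected, even when the true one is narrower.

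**Working it through.** **Inputs**

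- Number randomised: 60 (Sample size).
- Confidence level: 95% (Sample size; Statistical analysis).
- Illustrative rates: 20% attrition, 50% recruitment (Sample size).
- Number approached: not stated. Derived here as 60 divided by the assumed recruitment rate.

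**Step 1. Reproduce the plan's figures.** The usual normal-approximation half-width for a proportion is 1.96 × √(p(1−p)/n).

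- Attrition, p = 0.20, n = 60: 1.96 × √(0.16/60) = 10.1%, width 20.2%. The plan says ±10%, width 20%. This agrees, and 60 is the right denominator.
- Recruitment, p = 0.50, n = 60: 1.96 × √(0.25/60) = 12.65%, width 25.3%. The plan says ±12.5%, width about 25%. This agrees numerically.

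Other interval methods at p = 0.50, n = 60 give similar widths: Wilson 24.5%, Clopper-Pearson 26.4%.

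**Step 2. Back-solve the denominator.** Setting the half-width to 12.5% at p = 0.50 gives n = 1.96² × 0.25/0.125² = 61.5. The stated figure therefore corresponds to a denominator of about 60.

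**Step 3. Check this against the design.** With 60 as the denominator, 0.50 × 60 = 30 would be randomised, but the plan is to randomise 60. For 60 randomised at 50%, the denominator is 60/0.50 = 120. This holds whichever stage of the pathway is taken as the denominator (invited, interested or assessed), provided that the 50% refers to that stage.

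**Step 4. Recompute.** With p = 0.50, n = 120: 1.96 × √(0.25/120) = 8.9%, width 17.9%. Wilson gives a width of 17.6% and Clopper-Pearson 18.5%. If the 60 randomised are treated as fixed and the number approached as random, the half-width is 1.96 × √(p²(1−p)/60) = 1.96 × √(0.125/60) = 8.9%, the same. The half-width on 60 is √2 = 1.41 times the one that the design gives.

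**Step 5. Vary the assumed rate.**

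| Assumed recruitment rate | Approached (60/rate) | Half-width on that number | Half-width on n = 60 |
|---|---|---|---|
| 30% | 200 | 6.4% | 11.6% |
| 40% | 150 | 7.8% | 12.4% |
| 50% | 120 | 8.9% | 12.7% |
| 60% | 100 | 9.6% | 12.4% |
| 70% | 86 | 9.7% | 11.6% |

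The half-width with 60 randomised is proportional to √(p²(1−p)), which is largest at p = 2/3. There it equals 1.96 × √((4/27)/60) = 9.7%. No recruitment rate gives ±12.5% with 60 randomised.

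**The case against.** The strongest reply is that nothing depends on this figure. The true interval is narrower than the stated one, so the claim of reasonable precision is met more comfortably, and no sample size or threshold changes. That is correct, and it is why the point is minor. It does not make the stated width right.

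A second reply is that the denominator is inferred, since the article names a sample of 60 for attrition only. That is also true. But the back-calculation gives 61.5, no other number appears in the paragraph, and no rate reproduces ±12.5% with 60 randomised.

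A third reply is that a condensed article may leave the definition of a recruitment denominator to the full protocol or analysis plan. Agreed: the absence of a definition is not the finding. The finding is a stated number that conflicts with the number randomised in the same paragraph.

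A reader might also infer more than the article supports:

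- *That the justification for 60 fails.* It does not. Published suggestions and practicality come first, precision is an addition, and the attrition half is correct.
- *That the final analysis will report a wrong interval.* The Statistical analysis section fixes no denominator. Dividing 60 randomised by 60 would give 100%, which an analyst would notice.
- *That the progression criterion on recruitment contradicts this section.* Under Progression criteria, recruitment is judged against a target. That is a different use of the term, and no interval is attached to it. The two can stand side by side; clearer naming is a matter of preference.

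**Conclusion.** The point holds as a minor correction. The ±12.5% (width about 25%) is right arithmetic for a denominator of 60, but 60 is the numerator of the recruitment rate in this trial. With 60 randomised at an assumed 50%, the 95% interval is about ±9% (width about 18%). Across assumed rates of 30% to 70% the half-width is about 6.4% to 9.7%.

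This rests on two things: that recruitment rate here means the proportion of a larger pool who are randomised, and that the number approached, which the article does not give, equals 60 divided by the assumed rate. The error understates precision and leaves the sample size of 60 untouched.

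**What to change.** In the Sample size section, replace the recruitment sentence with wording such as: *Randomising 60 at a recruitment rate of around 50% implies about 120 potentially suitable young people invited, giving a 95% confidence interval of width about 18% (±9%).*

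In the Statistical analysis section, name the number of potentially suitable young people invited as the denominator of the recruitment-rate interval. This is preferable to a denominator of eligible young people invited: final eligibility is settled only after consent and the baseline assessment, so it is not confirmed for those who decline.

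The cost is one rewritten sentence and one added phrase, with no change to the sample size or to the analysis method. The article does not describe how invitations are counted, so the sponsor should confirm that the participating services can supply that count.

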### Randomisation

Randomisation will be coordinated remotely by the Norwich Clinical Trials Unit (CTU). Participants will be randomised in a 1:1 allocation ratio, using a stochastic minimisation algorithm to minimise imbalance between groups in baseline symptom severity, gender and study site. Allocation will be managed by the Data Management Team at Norwich CTU via a web-based system; it will not be accessible by anyone outside of this team, including the research team, trial therapists and participants; thus, allocation concealment will be maintained.

### Blinding

Research practitioners collecting follow-up data will be blind to the participant’s treatment allocation. Another member of the research team will pass details of allocation to the clinical service. Given the nature of the intervention, it will not be possible for participants and those involved in delivering the intervention to remain blind. Following allocation, all participants in the study and therapists will be asked not to reveal the group to which the participants were randomised to the research practitioner. Participants will be reminded at the beginning of each contact with the research practitioner post-randomisation not to disclose their allocation. Any potentially unblinding data will be stored separately in a database to which the research practitioner will not have access. In the case of accidental unblinding during the research process, a second research practitioner will complete the outstanding measures.

### Data collection

#### Outcome measures

Participants will be assessed at baseline (pre-randomisation) and followed up at 10 weeks and 23 weeks, with an additional 5-week follow-up (online with telephone support). The following outcome measures will be used: demographic characteristics of young person; Kiddie Schedule for Affective Disorders and Schizophrenia (K-SADS) depression section to assess for presence of DSM depressive disorders [30, 31]; Revised Children’s Anxiety and Depression Scale (RCADS) to assess self-rated severity of symptoms across depression, anxiety disorders and OCD [32]; Family Assessment Device (FAD) to measure quality of family relationships of participants [33]; Cambridge Friendships Questionnaire (CFQ), which measures quality of peer relationships of participants [34]; Employment, Education or Training in previous 4 weeks (NEET status), to capture levels of inactivity amongst young people who are not in work, education or training; Short Warwick-Edinburgh Mental Wellbeing Scale, which will measure mental wellbeing [29]; Modified Client Service Receipt Inventory (Modified CSRI), which will record information on service utilisation, income, accommodation and other cost-related variables [35]; and Health-related quality of life measured using the Child Health Utility 9D (CHU9D) [36].

The RCADS [32], FAD [33] and CFQ [34] will be repeated at an online week 5-follow-up. All outcome measures will be repeated at week 10 and 23 follow-up except for demographic characteristics of young person and the K-SADS depression section. Information about gender of therapist, attendance/non-attendance at planned therapy sessions and location of sessions will be collected by therapists in both treatment arms.

Table 1 shows the schedule of enrolment, interventions and assessments in accordance with the SPIRIT guidelines.

**Table 1 Tab1:**
[figure not shown]
SPIRIT Schedule of enrolment, interventions, and assessments

*The duration between initial screening and randomisation will vary depending on the time it takes a participant to complete baseline measures. However, we anticipate that all participants will be randomised within 4 weeks of their initial screening appointment

### Health economic data

We shall measure use of NHS and community resources related to mental health. All resources required to implement the intervention, including providing training, ongoing clinical supervision, staff time to deliver the intervention, any consumables and materials required and any other necessary expenditure will be captured. We will use a modified version of the Client Service Receipt Inventory (CSRI) [35] completed at each follow-up time point (baseline, 10 and 23 weeks). We shall use the CHU-9D [36] to measure health-related quality of life (HRQoL), which will be administered at baseline, week 10 and week 23.

### Process evaluation data

The trial will employ a mixed-methods ethnographic process evaluation to (a) provide a description of how IPC-A and TAU are delivered, (b) assess implementation and theoretical fidelity to the IPC-A model over time, (c) observe how delivery is shaped by the context of differing service models, (d) identify any harms arising from treatment (including end of treatment) and (e) establish the extent and source of any contamination of the control arm.

Data collection methods will include:
Site profile questionnaires (one per provider administered at the beginning and end of the trial)Observations of IPC-A training workshops and supervisionVideo/audio recordings of treatment sessions (both IPC-A and TAU; all treatment sessions will be recorded, subject to consent)Interviews with participants (young person and a parent/carer) from the IPC-A and TAU arms (*n* = 20)Focus groups with youth mental health workers (one per arm per provider)Focus group with wider stakeholders

#### Video/audio recording of treatment sessions

A random selection of therapy sessions (15% in each arm) will be rated by one of the supervisors according to the IPC-A Audiorecording Rating Scale [27], to monitor implementation fidelity to the IPC-A treatment model and to assess the degree of contamination. This scale includes ratings of techniques for the assessment (e.g. ‘Complete an Interpersonal Inventory’) and ending sessions, for specific focus areas (e.g. ‘Exploration and discussion of differences in expectations’ for relationship disputes), and general IPC techniques to be used for all sessions (e.g. ‘Clear focus on depressive symptoms and interpersonal relationships’).

Selection of sessions will be ongoing throughout the study. Feedback will be given to the therapist from the supervisor for IPC-A cases, to aid continued development. This process will be ongoing through the study so such feedback is timely. We accept that therapists in the TAU arm are less likely to submit sessions, but we shall regularly meet with teams and explain the importance of us rating sessions from both arms of the study, and that the aim of this is to check what TAU is and whether it contains IPC-A; the purpose is not to rate the quality of their therapy. Using findings from supervisor’s ratings of IPC-A sessions, a purposive sub-sample of extracts from recordings will also be selected (sampled to include maximum variation in delivery) and qualitatively analysed to evaluate theoretical fidelity.

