### Intervention: Interpersonal Counselling for Adolescents (IPC-A)

IPC-A is a brief manualised psychological intervention, derived from IPT. IPC helps clients to identify the reciprocal interaction between their current depressive symptoms and interpersonal relationships, with a focus on one of four domains: grief, relationship disputes, big changes, and loneliness and isolation. The therapist works with the client to identify effective strategies to deal with their interpersonal problems, which should improve depressive symptoms.

IPC-A is an adapted form of IPC designed to suit the needs of adolescents. The intervention is delivered over three to six (30–60 min) sessions, depending on participant needs. IPC-A is based on the manual developed by Weissman et al. [28]. The core interventions are the same as in the adult manual; however, language and examples are adapted to make them more relevant to adolescents. While we are testing efficacy of IPC-A, the manual is available for researchers interested in conducting research on it, on request from PW, the senior author of this paper. IPC-A arm participants will also have access to standard health and care provision (treatment as usual) throughout their participation, such as family work; the extent to which provision of IPC-A alters use of these services will be monitored using the Client Service Receipt Inventory (CSRI).

Staff to be trained as IPC-A therapists will receive two full days of initial training, followed by weekly supervision until adequate competency levels have been demonstrated (two sessions for each of two cases above quality threshold on IPC audiorecording rating scale [27]). Detailed training on complicated issues such as grief, and weekly supervision is likely to reduce harm from therapy (which will itself be asked about in the process evaluation). Following successful completion of this training, therapists will receive monthly clinical supervision. Where possible, supervision will be provided in a group format to allow therapists to explore the theory and practice of IPC through engaging in shared discussion of real-world cases. Each supervision session will last up to 1.5 h. Supervision will be delivered by PW, VC and ST, all trained IPT/IPC supervisors, with VC having overall responsibility for coordinating the provision of clinical supervision. Attendance at and costs of training and supervision will be recorded as therapy costs.

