### Progression criteria

#### Feasibility outcomes

The primary output of this feasibility trial will be the design of the subsequent full-scale trial. The TSC will assess the trial against the following criteria and make recommendations regarding the suitability of the proposed design for the full-scale trial, based on the extent to which these criteria are met.
Recruitment rate is at least 80% of targetAt least 70% of those randomised to receive the intervention attend at least three therapy sessions within the 10-week treatment windowFollow-up assessments are completed by at least 80% of participants at 10 weeks and 70% of participants at 23 weeksAt least 80% of IPC treatment sessions reviewed meet treatment fidelity criteriaContamination of the control arm can be sufficiently limited for individual randomisation to be justifiedThe mean RCADS depression scores of the IPC-A and TAU groups at 10 weeks are indicative of a clinically significant difference in depression (3 points)

The rate of completion of each outcome measure will be calculated and acceptability assessed via the process evaluation. We shall estimate the expected cost of the intervention and likely drivers of cost. The results of the feasibility study, the views of participants in the stakeholder focus group and guidelines from the Medical Research Council (MRC) on developing and evaluating complex interventions, will inform research design for subsequent research. If the proposed method is unable to limit contamination adequately, then a cluster trial or stepped wedge design will be considered. We will recommend an internal pilot study if outcomes from feasibility suggest that substantial changes to the protocol are required before progression. If the above criteria are met, we will apply for funding to progress to a multi-site, assessor-blind, RCT of the effectiveness and cost-effectiveness of IPC-A in comparison to TAU for adolescents presenting to non-specialist services with depressive symptoms, informed by our feasibility results.

Ultimately, if a future trial demonstrates IPC to be effective, an IPC-A training programme could be implemented nationally. This would facilitate rapid expansion of the therapy workforce, increasing access to evidence-based treatment for adolescent depression.

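### The session ratings behind the 80% fidelity criterion, and informing the contamination judgement, come from the IPC-A therapists' own supervisory team, so the fidelity result is exposed to lenient scoring

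*Protocol article*

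**What the plan says.** **Who rates, and what.** The section on video/audio recording of treatment sessions starts from "A random selection of therapy sessions (15% in each arm"). These sessions "will be rated by one of the supervisors according to the IPC-A Audiorecording Rating Scale", and the stated purpose is "to monitor implementation fidelity to the IPC-A treatment model and to assess the degree of contamination". One set of ratings therefore serves both questions.

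**What else the rating is for.** The same section adds: "Feedback will be given to the therapist from the supervisor for IPC-A cases, to aid continued development". This happens throughout the study and applies to IPC-A cases only.

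**Who the supervisors are.** The intervention section names three people who deliver IPC-A supervision, "all trained IPT/IPC supervisors". Weekly supervision continues until a therapist reaches a competency standard defined on the audiorecording rating scale: "two sessions for each of two cases above quality threshold on IPC audiorecording rating scale".

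**Where the ratings go.** The process evaluation analysis section uses the session ratings for fidelity and for contamination. The feasibility outcomes section lists six criteria. One is that at least 80% of reviewed IPC sessions meet fidelity. Another, with no number attached, is that contamination can be held low enough to justify individual randomisation. On how they are used: "The TSC will assess the trial against the following criteria and make recommendations regarding the suitability of the proposed design".

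**Masking.** The blinding section provides masking only for the research practitioners who collect follow-up data.

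**The concern.** A supervisor who scores a session from the IPC-A arm is partly scoring the product of their own supervision. The article does not separate the two roles. The scale that ends weekly supervision also supplies the evidence for fidelity, and the rating also leads to coaching feedback. Such a rater has an understandable reason to give a borderline session the benefit of the doubt. The article also identifies two of the three supervisors as having developed and piloted IPC-A.

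For TAU sessions the difficulty is expectation. TAU staff have had no IPC-A training, so a rater who knows the therapist knows the arm. That knowledge can colour the judgement of whether IPC-A content is present.

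Two of the six progression criteria draw on these ratings. The fidelity criterion depends on them directly. For contamination they act as the detector: interviews, observations and focus groups are to explore how contamination came about if it is identified. The answer bears on whether the full trial is individually randomised or moves to a cluster or stepped-wedge design.

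**Working it through.** **1. The plan's own precision figures.** The sample size section gives half-widths for 60 participants. With half-width = 1.96 × √(p(1−p)/n):
- attrition 20%: 1.96 × √(0.2 × 0.8/60) = 10.1% (stated 10%)
- recruitment 50%: 1.96 × √(0.5 × 0.5/60) = 12.7% (stated 12.5%)

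Both reproduce. The article gives no such figure for fidelity, no expected fidelity rate and no rater-agreement figure.

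**2. Number of rated IPC-A sessions.** Inputs: 60 participants randomised 1:1, so about 30 in IPC-A; 3 to 6 sessions each; 15% sampled. I assume that every participant completes and records 3 to 6 sessions, and that the sessions counted for the 80% criterion are this sample.
- 30 × 3 × 0.15 = 13.5, about 14
- 30 × 4.5 × 0.15 = 20.25, about 20
- 30 × 6 × 0.15 = 27

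Missed sessions or refused recording would lower these counts. The number of TAU sessions is not given, so no matching count is possible there.

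**3. What a pass requires.** Smallest whole number at or above 80%, with the Wilson 95% interval, and the count nearest to an assumed 70%:

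| Rated | Needed to pass | Wilson 95% CI at that count | About 70% | Ratings to change |
|---|---|---|---|---|
| 14 | 12 | 60% to 96% | 10 | 2 |
| 20 | 16 | 58% to 92% | 14 | 2 |
| 27 | 22 | 63% to 92% | 19 | 3 |

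**4. Sensitivity to leniency (illustration).** Let t be the true pass rate and f the share of failing sessions that are passed leniently. The observed pass probability is t + (1−t)f, and the chance of meeting the criterion is the binomial upper tail at the count needed. Both t = 70% and the values of f are my assumptions.

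| Rated | f = 0 (observed 70%) | f = 1/5 (76%) | f = 1/3 (80%) |
|---|---|---|---|
| 14 | 16% | 31% | 45% |
| 20 | 24% | 46% | 63% |
| 27 | 14% | 34% | 54% |

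Under these assumptions, leniency on one failing session in five about doubles the chance of a pass, and on one in three about triples or quadruples it.

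**The case against.** The other side has real force on several points.

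- **Progression is not decided by these ratings.** A reader might infer a go/no-go rule. The article has the TSC make recommendations across six criteria according to how far each is met. The ratings supply one criterion and inform another.
- **Upward bias is not shown.** It is tempting to say that the 80% figure is biased upward. Nothing in the document gives the size or direction of any bias. Lenient scoring is a risk and no more.
- **The direction for contamination is unknown.** One might infer that raters will under-score IPC-A content in TAU. A supervisor listening for that content could equally over-detect it, because some general items on the scale could occur in ordinary counselling. The contamination question is also put to the wider process evaluation.
- **The supervisors are not said to be the trainers.** The text reads "Staff to be trained as IPC-A therapists will receive two full days of initial training" without saying from whom. Only the supervisory link is documented.
- **Own-supervisee rating is permitted, not required.** Any of three supervisors may rate, and a fuller protocol could settle who rates whom.
- **Safeguards exist.** Sessions are chosen at random and scored on a structured scale.
- **Small numbers do much of the damage.** With an accurate rater and a true rate of exactly 80%, the chance of meeting the criterion is still only 45%, 63% or 54% for 14, 20 or 27 sessions.

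What remains is narrower. The choice of supervisors as raters is stated here, so it is not a detail merely left to another document. Random selection and a structured scale do not address who does the scoring. Small numbers add to the problem, because they leave little margin to absorb even mild leniency.

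**Conclusion.** The point holds in a limited form. The fidelity ratings behind the 80% criterion, and the session ratings that inform the contamination judgement, are made by the people who supervise the IPC-A therapists. The scale is also the one used for competency sign-off, and the text leaves a supervisor free to score their own supervisee knowing the arm. The fidelity result is therefore at risk of lenient scoring, and the contamination ratings are open to expectation bias of unknown direction.

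On size, two or three ratings out of about 14 to 27 would move an assumed 70% to a pass. This rests on all 30 participants having 3 to 6 recorded sessions, and on a 70% starting rate that the document does not supply. The randomised comparison on self-rated RCADS depression is not touched. This is a design choice worth tightening, not an error that undermines the study.

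**What to change.** In the section on video/audio recording of treatment sessions, state that:

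1. each sampled session is rated by one of the three supervisors who does not supervise that therapist;
2. files are relabelled without therapist name or arm, and IPC-A and TAU sessions are presented mixed;
3. the score is locked before any feedback, which still reaches the IPC-A therapist promptly through the usual supervisor;
4. a second supervisor re-scores a subset from each arm, and agreement is reported to the TSC beside the 80% figure, with the number of sessions rated.

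**Cost.** No new staff are needed. The work is file relabelling and a few double ratings. A small subset will reveal only gross disagreement, so its size should be given with the result.

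**Limits.** Masking from audio will be imperfect, since voices may be recognised and IPC-A content can itself reveal the arm. The raters also remain within the supervisory team. Supervision is planned in groups where possible; where this means that every supervisor knows a therapist, report it as a limitation.
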